#### Provisions for post-trial care {30}

There are no specific provisions for ancillary and post-trial care. In case of suffering harm from trial participation, a dedicated trial insurance will cover compensations.

#### Outcomes {12}

The primary endpoint is the need for transfusion of at least one unit of PRBCs. This is a valid and easily available functional parameter mirroring the immediate clinical implications of blood loss and has direct relevance on patients’ health status.

Secondary endpoints are the number of transfused units per participant, the time between skin incision and beginning of transfusion, the estimated intraoperative blood loss, operation/anesthesia times, D-dimer levels before and after the operation, hemoglobin levels before and after the operation, duration of hospital stay, quality of life, and postoperative complications and mortality.

The number of transfused units per participant, estimated intraoperative blood loss, and time between skin incision and beginning of transfusion represent measures for assumed reduction and deceleration of bleeding. The operation and anesthesia times might be shorter with reduced bleeding. D-dimer levels are a pro-coagulation state measure and hemoglobin levels reflect the amount of blood loss. Duration of hospital stay, quality of life, and postoperative complications and mortality mirror the clinical impact of hemorrhage and transfusion.

#### Participant timeline {13}

Schedule of enrolment, interventions, and assessments are shown in the table below.

**Table Taba:** 

	**Study period**				
	**Screening**	**Enrolment and allocation**	**Post-allocation**		**Close-out**
**Timepoint**	*** − 14 to − 1 days***	**0**	***Operation***** + *****Intervention***	***1st post-operative day***	***Day of discharge, max. 30th post-operative day***
**Enrolment:**					
**Eligibility screening**	X				
**Informed consent**	X				
***Routine laboratory parameter screening***	X	(X)			
**Allocation**		X			
**Interventions:**					
***Preoperative bolus 1000 mg TXA/10 min i.v. followed by intraoperative continuous infusion of 125 mg TXA/hr i.v. or placebo (normal saline solution)***			X		
**Assessments:**					
***Routine laboratory examination***^b^	X	(X)^a^		X	X
***Safety assessments (AE/SAE/AESI)***			X	X	X
***Transfusion Necessity***			X	X	X
***Concomitant medication***			X		
***Estimated intraoperative blood loss***			X		
***Operation***** + *****anesthesia duration***			X		
***Number of transfused PRBCs***			X	X	X
***Time to transfusion***			X	X	X
***Postoperative complications/mortality***			X	X	X
***Duration of stay***					X
***Quality of life (SF-12)***		X			X

^a^Pregnancy test: urine or blood beta-HCG within 72 h preoperatively in women of childbearing age

^b^Routine laboratory examinations: complete blood count, sodium, potassium, calcium, creatinine, and estimated GFR (MDRD formula), bilirubin, ALAT, ASAT, INR, apTT, D-Dimer levels

#### Sample size {14}

The sample size calculation is based on the assumption derived from the literature and own hospital data that in the control group (placebo), 30% of participants require intra- or postoperative transfusion of at least one unit of PRBCs [1, 29], and that the intervention (TXA) achieves a relative risk reduction of 33% [18], reducing the probability to 20%. This difference would not only be expected, but also represents a clinically meaningful value. With a type one error (alpha) of 5% and a power of 90%, using a two-sided *χ*^2^ test, this results in 412 participants per group (Software PASS).

Given that the primary endpoint is ascertained at the end of each participant’s hospital stay, virtually no loss to follow-up is expected. Non-compliance, i.e., withdrawal of consent during the study period, i.e., the hospital stay, is expected in 3% of patients, resulting in 425 participants per group to be randomized.

#### Recruitment {15}

Previous trials conducted in fields other than abdominal surgery support the notion that the randomization of a large number of patients between receiving TXA or not is feasible in a short time frame as long as the case volume in the respective study center is sufficiently high [19]. All participating centers are high-volume institutions in abdominal surgery, having relevant case volumes. All eligible participants planned for major abdominal surgery in the trial sites will be screened for and actively offered trial participation. Thus, complete trial recruitment within 18 months is deemed feasible.

### Assignment of interventions: allocation

#### Sequence generation {16a}

Participants will be randomized within 24 h prior to surgery in a 1:1 ratio to the TXA or the placebo group. Randomization will be stratified by planned surgical access (open vs. minimally invasive) and planned operation (esophagectomy, gastrectomy, colectomy, rectal resection, pancreatic resection, or hepatectomy). Randomization will be done via an online tool (secuTrial®) generating a randomization number.

#### Concealment mechanism {16b}

Randomization via an online tool (secuTrial®) generating a randomization number will ensure that group assignment is unbiased and concealed from participants, treating physicians, investigators, and other study staff. The online tool will provide the randomization number, which is identical to the Study Medication Number/reference code of the investigative medicinal product (IMP) label. All vials with study medication look identical, so that it remains concealed if participants receive TXA or placebo.

#### Implementation {16c}

The online randomization tool (secuTrial®) will generate the allocation sequence and assign participants to interventions by means of providing a randomization number. Participants will be screened and enrolled by investigators at the trial sites. The assignment of participants to the intervention or control arm will be blinded and done by randomization via the online randomization tool.

### Assignment of interventions: blinding

#### Who will be blinded {17a}

Trial participants, treating physicians, investigators, and other study staff will all be blinded regarding assignment to interventions.

#### Procedure for unblinding if needed {17b}

Only in case of an urgent medical reason (e.g., intraoperative disseminated bleeding in which a therapeutic use of TXA is deemed indicated), unblinding is possible. Such unblinding can be done by opening the appropriate blinding envelope upon due justification by the site investigator. The sponsor must be informed by fax about unblinding and its justification immediately (within 24 h). After unblinding, the treating physicians are informed about the participant’s allocation to TXA or placebo and can act according to the best individual therapeutic practice.

### Data collection and management

#### Plans for assessment and collection of outcomes {18a}

All data of trial participants are assessed and collected by investigators and study nurses. Study visits take place upon recruitment (14 days to 1 day prior to surgery), on the day of surgery, on day 1 after surgery, and on the day of hospital discharge or postoperative day 30, whatever occurs first. Trial staff is specifically trained for data assessment and collection. Data on the primary endpoint, PRBC transfusion, is extracted from specific transfusion files and patient files or hospital information systems. Laboratory data is extracted from the laboratory systems of the trial sites. Validation certificates for the single laboratories need to be provided. Clinical data including intraoperative data are collected from patient files or hospital information systems. Quality of life is measured with the validated German version of the SF-12 questionnaire. The questionnaire is handed out to trial participants and collected by study staff after it has been filled by the participant. All collected data will be documented in the study-specific electronic case record form (eCRF) as promptly as possible. Any entry in the eCRF has to be traceable to the information contained in the source data. eCRF templates are available upon request from the principal investigator.

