## Methods: participants, interventions, and outcomes

### Study setting {9}

The study is conducted at eleven academic hospitals in Germany. A list of all currently enrolled centers can be obtained on the European Medicines Agency website and at ClinicalTrials.gov.

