#### Plans for collection, laboratory evaluation, and storage of biological specimens for genetic or molecular analysis in this trial/future use {33}

Not applicable. The trial design does not foresee any collection of biological specimens.

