### Statistical methods

#### Statistical methods for primary and secondary outcomes {20a}

The primary endpoint will be compared in the intention-to-treat population between the two study arms with a logistic regression model including the treatment group, and the stratification variables type of operation (esophagectomy, gastrectomy, colectomy, rectal resection, pancreatic resection, hepatectomy) and type of planned surgical access (open, minimally-invasive) as covariates.

The secondary endpoints of postoperative in-hospital complications and mortality will be analyzed similarly. The number of transfused units of PRBCs, estimated intraoperative blood loss, length of hospital stay, operation time, anesthesia time, D-dimer levels, and quality of life will be analyzed using a linear regression model including treatment group, type of operation, and type of surgical access as covariates. In case of heavy skewness in the outcome data, the outcome variables will be transformed to reduce skewness. All results for secondary outcomes will be interpreted in an exploratory sense. Dichotomous outcomes will be reported as absolute and relative frequencies and continuous variables by means, medians, standard deviations, and ranges. Time to transfusion will be compared between both arms using time-to-event analysis.

A safety analysis will be carried out by comparing the frequency of all adverse events and adverse events attributed to the intervention between the two study arms. Patients with a history of thromboembolic events will be analyzed as a subgroup of special interest.

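### D-dimer comes from the local laboratories of eleven sites but is modelled without a site or laboratory term; a site factor on the log scale would protect precision at almost no cost

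*Protocol article*

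**What the plan says.** The Outcomes section {12} of the protocol article lists "D-dimer levels before and after the operation" among the secondary endpoints, and the abstract counts D-dimer among the key ones. The footnote to the participant timeline puts it with the routine laboratory tests: "bilirubin, ALAT, ASAT, INR, apTT, D-Dimer levels". Those tests are scheduled at screening, on the first postoperative day and at close-out.

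On where the values come from, section {18a} says: "Laboratory data is extracted from the laboratory systems of the trial sites. Validation certificates for the single laboratories need to be provided". Section {9} gives the number of sites: "The study is conducted at eleven academic hospitals in Germany". Central re-measurement is not foreseen; section {33} states: "The trial design does not foresee any collection of biological specimens".

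On the analysis, section {20a} says that D-dimer, with several other outcomes, "will be analyzed using a linear regression model including treatment group, type of operation, and type of surgical access as covariates". Outcomes are transformed only if heavily skewed, and all secondary results are to be read as exploratory. Section {16a} on sequence generation says: "Randomization will be stratified by planned surgical access (open vs. minimally invasive) and planned operation". Site is not named as a stratum.

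**The concern.** The article names a specific covariate list for D-dimer, and that list has no term for the laboratory that produced the value. A validation certificate shows that a laboratory's method is sound on its own terms. It does not show that two laboratories would return the same number for the same sample.

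If laboratories differ by a constant factor, the planned model has nowhere to put the difference except the residual. Site is known for every patient, so this loss can be avoided. Two things are at stake: the precision of the D-dimer comparison, and the meaning of a pooled mean or mean difference on the raw scale. The primary endpoint is not affected.

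**Working it through.** **Figures in the plan.** The article gives no SD, effect size or assay information for D-dimer, so there is no D-dimer figure to reproduce. The primary-endpoint sample size supplies only the patient count: 412 per group, 412/0.97 = 424.7, rounded up to 425, hence 850 randomized. The number of sites, 11, is from section {9}.

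**Assumptions (not in the documents).** Patient log-SD 0.7 (variance 0.49), pre-post correlation 0.4, and a laboratory effect that is a constant multiplicative factor per site. Two settings:
- (a) one unit everywhere, calibration log-SD 0.2 or 0.3 between sites;
- (b) in addition to calibration log-SD 0, 0.2 or 0.3, a twofold unit difference at 4 of 11 sites, left unconverted.

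**Step 1: between-site variance B on the log scale.**
- Calibration only: B = SD² × 10/11, which is 0.0364 (SD 0.2) or 0.0818 (SD 0.3).
- Twofold unit at 4 of 11 sites: B = (ln 2)² × (4/11)(7/11) = 0.111. Adding calibration gives 0.148 or 0.193.

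**Step 2: variance of the treatment effect, no site term versus site term.** The ratio is roughly 1 + B/0.49. Dividing by 1 + 10/850 = 1.012 allows for the 10 degrees of freedom that the site factor uses.

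| Setting | 1 + B/0.49 | after division by 1.012 | simulated (850 patients, 600 replicates) |
|---|---|---|---|
| One unit, calibration 0.2 | 1.07 | 1.06 | 1.06 |
| One unit, calibration 0.3 | 1.17 | 1.15 | 1.15 |
| Twofold, calibration 0 | 1.23 | 1.21 | 1.21 |
| Twofold, calibration 0.2 | 1.30 | 1.29 | 1.29 |
| Twofold, calibration 0.3 | 1.39 | 1.38 | 1.38 |

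**Step 3: the same with the preoperative value in both models.** Without site, the residual variance is (0.49 + B) − (0.4 × 0.49 + B)²/(0.49 + B). With site it is 0.49 × (1 − 0.4²) = 0.412. For B = 0.0818 the first is 0.437, so the ratio is 1.06, or 1.05 after division by 1.012. The simulated ratios are 1.02 and 1.05 with one unit, and 1.07, 1.09 and 1.11 with the twofold unit. The baseline removes most of the laboratory factor but not all of it.

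**Step 4: sensitivity to the patient SD.** At log-SD 1.0 the denominator is 1.0. The ratios after division fall to 1.02 and 1.07 (one unit) and to 1.10 (twofold, no calibration difference; 1.11 before division).

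**Step 5: power and type I error.** A separate simulation used 824 patients (2 × 412), 11 sites, within-site log-SD 0.8, log effect −0.2 and 1,500 runs per scenario. Power on the log scale, without versus with site terms:
- no site difference: 0.95 versus 0.94 (0.949 and 0.943 before rounding);
- between-site log-SD 0.35: 0.91 versus 0.95;
- twofold factor at 5 of 11 sites: 0.90 versus 0.94.

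Type I error without site terms was 0.045 to 0.057 in every scenario, raw-scale ones included. On the log scale the mean estimate stayed at about −0.20 throughout.

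**Step 6: the raw scale.** With the same log effect, the raw mean difference is exp(0.32) × (exp(−0.2) − 1) = −0.25 without site differences. With a factor of 2 at 5 of 11 sites it is multiplied by 1 + 5/11 = 1.45, giving −0.36 (simulated −0.37). The simulated estimate is the same with site terms in the model. A site term on untransformed values therefore does not restore a common scale.

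**The case against.** The best case for the plan has four parts.

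1. Nothing in the article says that assays or units differ. A reader might infer that the pooled levels have no common scale and that their summaries cannot be interpreted. The documents do not support that; it would follow only if the laboratories were shown to differ. This objection stands in full.

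2. Recording and converting units belongs to the eCRF, the data management documents or the SAP, none of which is shown. Section {19} describes electronic plausibility and consistency checks, which may catch gross unit errors. This also stands, so a missing conversion rule cannot be held against the article, and the 21 to 38% figure describes a failure that nothing shows will happen.

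3. Adjusting for the stratification factors is coherent, and the endpoint is exploratory. A reader might infer that chance imbalance of arms across sites distorts the result. It does not: randomization prevents systematic bias, the imbalance is ordinary sampling error already reflected in the standard error, and the simulated type I error is nominal. What survives is the loss of precision.

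4. A within-patient log change would cancel a constant laboratory factor without a site term. That is correct, but section {20a} does not specify a change score. At the assumed correlation of 0.4 its variance is 2 × 0.49 × (1 − 0.4) = 0.588, against 0.412 for the baseline-adjusted model with site.

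**Conclusion.** The point holds as a modest, conditional improvement to a model that the article does state. If the laboratories differ by a constant factor, leaving site out makes the variance of the D-dimer treatment effect about 6 to 15% larger with one reporting unit, or 2 to 5% larger if the preoperative value is also in the model. The 21 to 38% range (7 to 11% with the preoperative value) applies only to an unconverted twofold unit difference at 4 of 11 sites. These figures rest on a patient log-SD of 0.7 and a correlation of 0.4, both assumed, and they fall as the patient SD rises. In power terms, the simulated between-site differences (log-SD 0.35, or twofold) cost about 4 points.

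There is no bias between arms, no type I error inflation and no consequence for the primary endpoint. If the analysis stays on the raw scale and laboratories differ, the mean difference also depends on the mix of scales, which a site term alone does not repair.

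**What to change.** In section {20a}, and in the SAP to match, take D-dimer out of the shared linear-model sentence. Specify log D-dimer as the outcome, with treatment, operation, access, site (standing for laboratory) and the log preoperative value as covariates. Report the treatment effect as a ratio of geometric means with its confidence interval. Choosing the log scale in advance also replaces the data-dependent skewness rule for this outcome.

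The preoperative value is already in the assessment schedule and site is known for every patient, so no new data are needed. The site factor uses 10 degrees of freedom out of about 850 patients. If laboratories agree, it costs about one point of power (0.95 to 0.94 in the simulation).

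Separately, confirm in the eCRF or SAP that assay and unit are recorded per site and that values are converted to one unit. This is a point to check, not a deficiency of the article.

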#### Plans to promote participant retention and complete follow-up {18b}

Given that the primary endpoint is ascertained at the end of each participant’s hospital stay, virtually no loss to follow-up is expected. Non-retention, i.e., withdrawal of consent during the hospital stay is not expected in a relevant proportion of participants. If participants decide to withdraw from the trial, complete collection and documentation of outcome data will still be sought if the participant agrees.

#### Data management {19}

Investigators or designated persons will document the study data in the study-specific eCRF as promptly as possible. Any entry in the eCRF has to be traceable to the information contained in the medical file and the source data. The data will be entered directly at the study site by the site staff via remote data entry in the study-specific eCRF in English. The study management software secuTrial (iAS GmbH, Berlin, Germany), a validated database-driven complete solution for the conduction of clinical studies, will be used for data entry and query management (cooperation between Coordination Center for Clinical Trials [KKS] Halle and Center for Clinical Trials [ZKS] Leipzig).

Management of the study data base will be done by KKS Halle. All changes in the data will be recorded by an audit trail. The study software provides an adaptive concept for user accounts and user roles depending on the study. The data base is integrated in a general IT infrastructure and security concept including a firewall and backup system. The data will be saved on a daily basis by ZKS Leipzig. In a multistage procedure, the obtained data will be checked electronically for their plausibility and consistency by KKS Halle. In case of implausible or missing data, queries will be generated and provided to the investigator in order to obtain any missing information and resolve inconsistencies. After completion of data capture and quality check the data base will be closed by KKS Halle and the data will be transferred to the biometrician for statistical analysis.

#### Confidentiality {27}

Information about study patients will be kept confidential and managed under the applicable laws and regulations. All investigators must ensure data protection of the patients; Patients must not be identified by names in any documents submitted to the sponsor. Signed informed consent forms and patient identification logs must be kept strictly confidential to enable patient identification at the site. All study-related information is stored securely at the study site. On any document that is submitted to the sponsor, subjects shall be identified by the unique Patient-ID only (pseudonymized). It must be ensured that the Sponsor and KKS Halle do not receive any data that would allow conclusions to be drawn about the identity of the person concerned.

#### Plans for collection, laboratory evaluation, and storage of biological specimens for genetic or molecular analysis in this trial/future use {33}

Not applicable. The trial design does not foresee any collection of biological specimens.

### Statistical methods

#### Statistical methods for primary and secondary outcomes {20a}

The primary endpoint will be compared in the intention-to-treat population between the two study arms with a logistic regression model including the treatment group, and the stratification variables type of operation (esophagectomy, gastrectomy, colectomy, rectal resection, pancreatic resection, hepatectomy) and type of planned surgical access (open, minimally-invasive) as covariates.

The secondary endpoints of postoperative in-hospital complications and mortality will be analyzed similarly. The number of transfused units of PRBCs, estimated intraoperative blood loss, length of hospital stay, operation time, anesthesia time, D-dimer levels, and quality of life will be analyzed using a linear regression model including treatment group, type of operation, and type of surgical access as covariates. In case of heavy skewness in the outcome data, the outcome variables will be transformed to reduce skewness. All results for secondary outcomes will be interpreted in an exploratory sense. Dichotomous outcomes will be reported as absolute and relative frequencies and continuous variables by means, medians, standard deviations, and ranges. Time to transfusion will be compared between both arms using time-to-event analysis.

A safety analysis will be carried out by comparing the frequency of all adverse events and adverse events attributed to the intervention between the two study arms. Patients with a history of thromboembolic events will be analyzed as a subgroup of special interest.

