#### Exclusion criteria

Severe anemia, defined as a hemoglobin concentration < 8 g/dL (< 5 mmol/L) or anemia with hemoglobin concentration ≥ 8 to < 10 g/dL (≥ 5.0 < to < 6.2 mmol/l) and one or several of the following symptoms suggesting hypoxemia:Clinical signs of tachycardia, e.g., resting heart rate > 100 beats/min, palpitation, etc.Clinical signs of hypotension, e.g., resting systolic blood pressure < 100 mmHg, orthostatic dysregulation, etc.Clinical signs of dyspnea, e.g., speech dyspnea, resting respiratory rate > 20 breaths/min.Thrombocytopenia with platelets < 60 × 109/LConfirmed bleeding disorder with the need for specific preventive perioperative treatment (e.g., factor deficiency with the need for perioperative substitution)A priori refusal of blood transfusionsConfirmed thrombophilia with a pertinent need for perioperative anticoagulationAllergy/hypersensitivity to TXARecent (< 30 days) thromboembolic eventHistory of medically confirmed convulsionsIn female subjects: pregnancy or lactation.

All participating study centers are institutions with a vast experience in conducting larger abdominal surgery comprising esophagectomy, gastrectomy, colectomy, rectal resection, pancreatic resection, and hepatectomy. All study sites need to fulfill GCP requirements.

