#### Relevant concomitant care permitted or prohibited during the trial {11d}

All perioperative and operative procedures are carried out according to clinical standards. Treatment with anticoagulants (e.g., platelet inhibitors, direct oral anticoagulants, vitamin K antagonists) is in principle allowed according to clinical indication. However, all anticoagulants should be paused or bridged with low molecular weight heparin during the perioperative period according to national and local guidelines. Pro-coagulation treatments such as coagulation factors, fresh frozen plasma, platelet transfusions, and Factor XIII substitution can be administered according to the individual judgment of the treating physician.

In case of a thromboembolic event, appropriate treatment should be initiated according to national and local guidelines. This might include medical treatment (e.g., fibrinolysis, anticoagulation) as well as interventional and surgical treatment (e.g., thrombectomy, embolectomy). In this case, an AE/SAE must be reported.

Detailed recommendations for when transfusions should be given are provided to all trial sites based on the cross-sectional guidelines for therapy with blood components and plasma derivates of the German Medical Association [28], thus minimizing heterogeneity across centers with regard to the primary endpoint.

Basic patient blood management is ensured for all participants. Measures include education initiatives and standard operating procedures, massive hemorrhage protocols, coagulation and transfusion algorithms, an online PBM e-learning course for all involved staff, screening for, diagnosis, and treatment of preoperative anemia, intravenous iron if oral iron is not tolerated, postponement of elective surgery until preoperative anemia has been classified and possibly treated, reduction of iatrogenic diagnostic-/surgery-related blood loss, avoiding unnecessary laboratory tests, lower frequency and amount of sampling, cessation and bridging strategies for anticoagulation and antiplatelet therapy, appropriate intraoperative approaches (meticulous hemostasis, minimally invasive surgery, and diathermy dissection). A detailed patient blood management manual will be provided to all trial sites.

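### Free improvement: the primary logistic model could also adjust for preoperative hemoglobin, which is already measured, for a modest gain in power

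*Protocol article*

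**What the plan says.** Protocol article, Outcomes {12}: "The primary endpoint is the need for transfusion of at least one unit of PRBCs".

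Sequence generation {16a}: "Randomization will be stratified by planned surgical access (open vs. minimally invasive) and planned operation", with six operations and two types of access. Hemoglobin is not a stratification factor.

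Statistical methods for primary and secondary outcomes {20a}: the primary endpoint is compared in the intention-to-treat population "with a logistic regression model including the treatment group, and the stratification variables type of operation" and type of planned surgical access. The covariate list ends there.

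Three places show that hemoglobin is known before surgery:
- The first exclusion criterion begins "Severe anemia, defined as a hemoglobin concentration" and sets cut-offs, so a value is needed to establish eligibility.
- The footnote to the assessment schedule reads "Routine laboratory examinations: complete blood count, sodium, potassium, calcium, creatinine" and continues. These tests are marked at screening, in brackets at day 0, on the first postoperative day and at close-out.
- The secondary endpoints include "hemoglobin levels before and after the operation".

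The patient blood management measures in section {11d} include "screening for, diagnosis, and treatment of preoperative anemia". No section states how strongly hemoglobin predicts transfusion.

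**The concern.** The endpoint is receipt of red cells. A patient who starts with a lower hemoglobin reaches any given level after less bleeding, so preoperative hemoglobin can be expected to predict the outcome in both arms. Entry is possible from 8 g/dL upward in patients without the listed symptoms, so values will differ between patients. Neither the randomization nor the analysis uses this information.

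What is at stake is efficiency. In a logistic model, a prognostic baseline covariate raises the power of the treatment test and reduces the variance of a treatment effect standardized to the trial population. If hemoglobin is prognostic, the strata-only model forgoes that gain although the data are already being collected.

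**Working it through.** **Inputs from the protocol article, Sample size {14}:** control risk 0.30, TXA risk 0.20, two-sided alpha 5%, power 90%, χ² test, 412 per group, 3% non-compliance, 425 per group randomized.

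**Step 1. Reproduce the planned size.** Without continuity correction, with mean risk 0.25,

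n₀ = [1.960·√(2·0.25·0.75) + 1.2816·√(0.30·0.70 + 0.20·0.80)]² / 0.10² = (1.2002 + 0.7795)² / 0.01 = 391.9, so 392.

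With continuity correction,

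n = (n₀/4)·[1 + √(1 + 4/(n₀·0.10))]² = (391.9/4)·(2.0498)² = 411.7, so 412.

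Then 412/0.97 = 424.7, so 425. Both stated figures reproduce.

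**Step 2. Power at 412 before any change.** For the uncorrected χ² test,

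Φ[(0.10·√412 − 1.960·√0.375)/√0.37] = 0.914.

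The planned 90% is therefore met without hemoglobin.

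**Step 3. Add hemoglobin.** Each scenario used 4,000 simulated trials with 412 per group and marginal risks held at 30% and 20%. The stated model (treatment, six operations, access) was compared with the same model plus linear hemoglobin.

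Assumptions not taken from the documents:
- the odds ratio per SD lower hemoglobin, varied from 1.0 to 3.0
- equal shares of the six operations and two access types
- log-odds effects of 0, −0.1, −0.4, −0.4, 0.4 and 0.4 for the operations and ±0.3 for access
- normally distributed hemoglobin, independent of operation and access

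Relative efficiency is the squared ratio of (mean estimate / mean SE) with and without hemoglobin. The equivalent n is 412 divided by it.

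| OR per SD lower Hb | Power without | Power with | Relative efficiency | Equivalent n per group | Variance ratio, standardized risk difference |
|---|---|---|---|---|---|
| 1.0 | 92.2% | 92.3% | 1.00 | 412 | 1.00 |
| 1.25 | 91.9% | 92.4% | 1.01 | 408 | 0.99 |
| 1.5 | 91.6% | 92.5% | 1.03 | 401 | 0.97 |
| 2.0 | 92.5% | 94.6% | 1.08 | 380 | 0.93 |
| 2.5 | 91.9% | 94.8% | 1.14 | 362 | 0.88 |
| 3.0 | 92.1% | 95.7% | 1.19 | 347 | 0.85 |

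Monte Carlo error of each power is about 0.4 points. The differences between rows in the column without hemoglobin are of that order.

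**Step 4. Where the gain comes from.** At an odds ratio of 2.0 per SD, the treatment log odds ratio goes from −0.563 (SE 0.168) to −0.613 (SE 0.176). At 3.0 it goes from −0.558 (SE 0.167) to −0.673 (SE 0.185). The SE rises, but the conditional effect moves further from zero. At 3.0, (0.673/0.185)² / (0.558/0.167)² = 1.19. Precision improves only on the marginal scale, as the last column shows.

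**Step 5. A smaller treatment effect.** The background section cites a 22% relative reduction in transfusion after hip fracture surgery. Applied to 30%, that gives 0.30·(1 − 0.22) = 23.4%. At 412 per group the stated model then has about 58 to 60% power. With hemoglobin it reaches about 62 to 63% at an odds ratio of 2.0 per SD and about 66% at 3.0. At 1.5 the gain is between 1 and 2 points.

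**The case against.** The strongest objection is that nothing in the plan is wrong. The model is prespecified and adjusts for exactly the factors used in stratification. It has no bias or type I error problem, and at the planned effect it exceeds its power target. All of that stands, and it is why this is an improvement and not a defect.

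The size of the gain is also open. The exclusions at the low end and the preoperative treatment of anemia narrow the hemoglobin range. A screening value may be up to 14 days old and may predate that treatment. The weak-association rows, with gains of 1 point or less, are therefore realistic. This stands too, and it limits the size of the gain. It does not remove the case, because the simulation shows no loss when the association is absent.

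A reader might infer more than the documents support:
- *Hemoglobin strongly predicts transfusion in this trial.* No coefficient is given. The expectation is plausible, but its strength is an assumption.
- *The trial is underpowered without hemoglobin.* At 30% versus 20% it is not (Step 2).
- *The odds ratio becomes more precise.* Its standard error rises (Step 4).
- *Centre is needed as well.* Section {11d} mentions heterogeneity across centers only to say that common transfusion recommendations minimize it. The calculations here do not test a centre effect.
- *The mortality model needs the same covariate.* This was not examined, and a rare outcome may not support further terms.
- *Only an odds ratio will be reported.* Section {20a} also promises absolute and relative frequencies by outcome, and effect-measure details are commonly left to the SAP.

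**Conclusion.** The point holds as a free improvement. A baseline variable that is expected to be prognostic, and is available for every patient, is absent from both the stratification and the primary model.

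At the planned effect, adding it is worth 0 to 4 percentage points of power. Relative efficiency is 1.00 to 1.19, so the same power would need up to about 16% fewer patients (1 − 347/412). The variance of the standardized risk difference falls by 0 to 15%. The power gain is somewhat larger if the true effect is smaller than planned. These figures rest on the assumed odds ratios of 1.0 to 3.0 per SD and on the simulated mix of operations and access. The lower half of the range gives almost nothing.

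The plan remains valid if it is left unchanged.

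**What to change.** Before unblinding:

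1. Add preoperative hemoglobin to the primary logistic model as a continuous covariate, beside treatment, type of operation and planned access.
2. Define it as the last value before randomization, and state whether the screening or the day-0 value counts. The day-0 laboratory entry is bracketed, and in the assessments row that bracket carries the pregnancy-test footnote, so a repeat blood count cannot be assumed for everyone.
3. Report a standardized (marginal) risk difference with a 95% confidence interval beside the odds ratio. The sample size is framed as a fall from 30% to 20%, and this is the scale on which precision improves. State that the odds ratio is then conditional on hemoglobin as well as on the strata, so its size is not directly comparable with that from the strata-only model.
4. Keep the strata-only model as a named sensitivity analysis.

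No new data collection and no change in sample size are needed. The cost is a small protocol or analysis-plan amendment while recruitment, begun in June 2024, is under way. Because the protocol itself names the model, the sponsor would have to judge whether the change is a substantial modification that needs approval. Covariates chosen after unblinding would undermine the confirmatory test, so the change should be made before then or not at all.
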